## Methods

### Study Design

Our study is a prospective, multicenter cohort study conducted in a real-world setting. An overview of the study flowchart is presented in Figure 2. It is planned to enroll 2000 patients with AIS, as defined in the *Chinese Guidelines for Diagnosis and Treatment of Acute Ischemic Stroke 2018* [15] and *Stroke Diagnosis and Effectiveness Evaluation Standards* [16]. A total of 3 visits will be carried out within a 6-month follow-up period. Baseline demographic data, therapeutic effects, adverse events, and complications associated with DZHJTI will be analyzed.

**Figure 2 figure2:**
[figure not shown]
Flowchart of the study design. AIS: acute ischemic stroke; DZHJTI: Dazhu hongjingtian injection.

### Participants

To collect a representative sample, the nephrology departments of 30 secondary or tertiary hospitals in multiple regions of China will continuously recruit and enroll patients. Recruitment began in November 2022 and will continue until at least 2000 participants are recruited. Potential patients will undergo eligibility screening based on the inclusion and exclusion criteria. Eligible patients or their legally authorized representatives will provide written informed consent before undergoing any study-specific procedures. Textbox 1 provides detailed information on the inclusion and exclusion criteria.

Inclusion and exclusion criteria of the cohort study.
**Inclusion criteria**
Female or male patients aged ≥18 yearsMeeting the acute ischemic stroke diagnostic criteriaTime from symptom onset to the hospital admission ≤14 daysWillingly participates in the clinical study and signs the informed consent
**Exclusion criteria**
Clinically silent acute ischemic strokeMinor stroke or minor neurological deficit (National Institute of Health Stroke Scale score of 0-5), nondisabling or rapidly improving transient cerebral ischemiaSevere hypertension or diabetes that is still unable to control the disease after treatmentOther conditions that cause motor dysfunction (claudication, severe osteoarthrosis, rheumatoid arthritis, gouty arthritis, etc)Unable to complete daily activities independently due to various diseases and physical weakness before this disease, which seriously affects the effectiveness evaluationKnown complications affecting drug evaluation, including severe cardiac insufficiency, renal insufficiency, severe mental illness, depression after stroke, dementia, cerebral hemorrhage after cerebral infarction, and so forthKnown contraindications of Dazhu hongjingtian injection: pregnancy, allergic constitution, multiple drug allergies, allergy to ingredients in Dazhu hongjingtian injection, known adverse reactions to any component of the Dazhu hongjingtian injectionControls who used other dosage forms of Dazhu hongjingtian injection (tablets, capsules, etc)Unsuitability for participation as judged by the investigators

### Treatment Regimens

All patients will receive current guideline-recommended treatments according to *Chinese Guidelines for the Diagnosis and Treatment of Acute Ischemic Stroke 2018* [15]. The most commonly used medications and treatments include intravenous thrombolysis drugs, antiplatelets, anticoagulants, drugs for volume expansion, neuroprotectants, medicines for improving cerebral blood flow, and traditional Chinese medicine. Cases will be recruited from patients who receive DZHJTI according to the physician’s order. The DZHJTI will be manufactured and supplied by Tonghua Yusheng Pharmaceutical Co, Ltd (approvals Z20060361 and Z20060362), with identical appearance, color, and flavor. The fingerprint-based quality control and ingredient identification met the Chinese pharmacopeia’s reference requirements (detailed information is provided in Multimedia Appendix 1). The administration and dosage of DZHJTI will be determined by the attending physicians based on the patients’ medical history and clinical manifestations.

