**Methods:**

This prospective, multicenter cohort study plans to enroll 2000 patients with AIS within 14 days of symptom onset from 30 hospitals across China. Eligible patients will be followed up for 6 months after initiating medication treatments. The primary outcome will be the change in the National Institute of Health Stroke Scale score from baseline to outpatient follow-up. The secondary outcomes include overall mortality, stroke recurrence, new-onset major vascular events, global disability, and improvement of traditional Chinese medicine syndrome in 6 months. Adverse events or clinically significant changes in vital signs and laboratory parameters, regardless of the severity, will be recorded during the trial to assess the safety of DZHJTI. An augmented inverse propensity weighted estimator will be used to reduce variability and improve accuracy in average treatment effects estimation.

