### Data Collection and Monitoring

Trained research personnel at each participating site will collect baseline data during patient admission, including prehospital care and treatment, prestroke symptoms, and the NIHSS. They will also conduct assessments using the prestroke modified Rankin Scale scores and Barthel Index. Patient information, including demographics, medical and family history, physical examination, auxiliary examination, risk factor assessment, and clinical diagnosis, will be obtained from medical records. The classification of stroke etiology, related complications, and new cerebrovascular events will be documented, and the etiology of AIS will be determined according to the Trial of Org 10172 in Acute Stroke Treatment criteria [17]. Besides standard therapies, the administration of DJHJTI during hospitalization will be documented by the research team.

The collection and reporting of data will use a secure electronic data capture (EDC) system that follows the current clinical protocol and provides each patient with a unique ID. Authorized research personnel can access the EDC system both on personal computers and smartphones, enabling them to complete data collection during daily ward rounds. An overview of the measurement data collection schedule is shown in Table 1. In the EDC system, personal identifiers such as names, ID numbers, and contact information are removed or replaced with unique codes to ensure participant anonymity.

**Table 1 table1:** Schedule of assessments in the cohort study.

Participant assessment	Time point and form				
	Baseline (acute phase)		Follow-up 1	Follow-up 2	Follow-up 3
	Admission	Discharge	1 month	3 months	6 months
	Visit	Visit	Visit or telephone interview	Visit or telephone interview	Visit or telephone interview
Eligibility screen	✓^a^				
Informed consent	✓				
Demographic and anthropometric data	✓				
TCM^b^ questionnaire	✓				
NIHSS^c^	✓	✓			
mRS^d^	✓	✓	✓	✓	✓
BI^e^			✓	✓	✓
Laboratory examination	✓	✓	+^f^	+	+
Imaging examination	✓	✓	+	+	+
Admission status		✓			
Discharge status		✓			
Follow-up interview			✓	✓	✓
AE^g^		+	+	+	+
Outcomes		+	+	+	+

^a^Required data.

^b^TCM: traditional Chinese medicine.

^c^NIHSS: National Institutes of Health Stroke Scale.

^d^mRS: modified Rankin Scale.

^e^BI: Barthel Index.

^f^Optional data to be collected based on the actual occurrence of related events in patients.

^g^AE: adverse events.

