### Follow-Up Procedures

All patients will be identified and followed up using individual identity cards, which are mandatory for all Chinese citizens, enabling unambiguous linkages. Research personnel will conduct regular face-to-face or telephone follow-up at 1, 3, and 6 months after stroke onset. Information on patient outcomes, including mortality, functional status, activities of daily living, cognitive function, and cardiovascular or cerebrovascular events, will be obtained during follow-up. Mortality will be confirmed through a death certificate issued by the local civil registry or the attending hospital. New cardiovascular or cerebrovascular events requiring rehospitalization will be verified by the discharge diagnosis. In the absence of hospitalization, a committee responsible for determining end points will evaluate suspected recurrent cardiovascular or cerebrovascular events [18].

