**Primary outcome**		
	Improvement degree of clinical NIHSS^a^ scores	Basic recovery (NIHSS score decreased by more than 90%) Significant improvement (NIHSS score decreased by 46%-89%) Improvement (NIHSS score decreased by 18%-45%) No change (NIHSS score decreased 0%-18% or increased<18%) Deterioration (NIHSS score increased more than 18%) The basic recovery, significant improvement, and improvement were regarded as effective. The no change, deterioration, and death were regarded as inefficient [19]

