However, it is important to note that biases are common in real-world studies. Participants from different study sites may differ in characteristics, and combined treatments can vary widely. Additionally, incomplete data can be a significant issue with real-world data sources. Therefore, we plan to use the AIPW estimator, which involves a doubly robust procedure to minimize bias if either the treatment or outcome model is correctly specified [27]. The accuracy of the AIPW estimator for the average treatment effect has been demonstrated under different scenarios of misspecification [27]. To perform propensity score analysis when data are missing, we will conduct the analysis in each imputed data set and then combine the estimates of the treatment effect to obtain an overall estimate. This method has been demonstrated to be unbiased under a missing at random mechanism, and Rubin rules have been shown to provide reliable variance estimates and show good balancing properties [20].

Another key consideration in this trial is selecting an appropriate primary outcome, which depends largely on the disease and should reflect the treatment effect and expected mechanism. NIHSS is a tool used to objectively quantify neurological impairment after stroke [28], while the modified Rankin Scale and modified Barthel Index are commonly used scales to measure disability or dependence in daily activities in patients with stroke or other neurological dysfunction [29]. Previous studies on herbal injection often have limited follow-up periods of up to 3 months due to drug metabolism. However, since AIS neurological function recovery is a slow process, with the main recovery period occurring within 2 to 6 months after onset [30], we evaluated the effects of DZHJTI on neurological recovery for a period of 6 months after discharge from the hospital.

To our knowledge, this is the first and largest prospective cohort study in China that evaluates the real-world effectiveness and safety of DZHJTI in the treatment of AIS. It may provide additional clinical evidence, including the duration of response, long-term drug effectiveness, and subgroup efficacy data of DZHJTI treatment for patients with AIS under the influence of other confounding factors. Ultimately, the results of this study will help optimize individualized interventions with DZHJTI for the treatment of AIS in China, leading to better patient outcomes and more standardized treatment practices.

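### Three conflicting starts for the 6-month follow-up and no common index date for the two groups, which risks immortal-time bias in favour of DZHJTI for mortality

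*Protocol article*

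**What the plan says.** **Time origin.** The article gives three:
- Abstract, Methods: "Eligible patients will be followed up for 6 months after initiating medication treatments". It does not say which medication starts the clock.
- Methods, Follow-Up Procedures: "face-to-face or telephone follow-up at 1, 3, and 6 months after stroke onset".
- Discussion, on the choice of outcome: effects are evaluated "for a period of 6 months after discharge from the hospital".

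Table 1 labels the visits only as 1, 3 and 6 months, so it does not settle the matter. Textbox 1 allows admission up to 14 days after symptom onset.

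**Exposure.** Under Treatment Regimens, "Cases will be recruited from patients who receive DZHJTI according to the" physician's order. Administration and dosage are left to the attending physician. Under Data Collection and Monitoring, "the administration of DJHJTI during hospitalization will be documented by the research team". No window for the first dose and no matching date for controls is given. Table 1 places the eligibility screen, informed consent and baseline NIHSS at admission.

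**Outcomes and analysis.** In Table 2, under the primary outcome, "The no change, deterioration, and death were regarded as inefficient". Overall mortality is the first secondary outcome listed. Statistical Analysis names Kaplan-Meier, Cox regression, AIPW, multiple imputation and a sensitivity analysis for unmeasured confounding. It states no time zero.

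**The concern.** A cohort comparison of a treatment with no treatment is interpretable when eligibility, group assignment and start of follow-up coincide for both groups. Here baseline is at admission, group membership depends on something that may happen later in the stay, and the start of follow-up is given in three ways.

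If some orders come days after admission, patients in the DZHJTI group have by definition survived to that order. Controls carry no such condition, so early deaths can fall only among controls, or be missing only from the DZHJTI group. Mortality then looks lower with DZHJTI even if the drug does nothing. Death also counts as failure in the primary outcome, so the problem can reach that analysis too.

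The conflicting clocks have a second consequence. Sites following different sentences would hold the visits of the same name at different disease times.

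**Working it through.** The article gives no figure for this point, and its sample-size calculation does not bear on it. The check therefore has two parts: how far the clocks can differ, and what receipt-based exposure does when there is no true effect.

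**1. Clocks.** Admission may fall on day 14 after onset (Textbox 1), so onset and in-hospital treatment start can differ by 14 days or more. Assume also a 14-day stay, which the article does not give. Discharge is then on day 14 + 14 = 28. One month after onset (day 30) is 2 days after discharge, and month 6 from discharge falls 28 days later than month 6 from onset. This is the wide end; admission on the day of onset and a short stay give a small shift.

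**2. Mortality with no drug effect.** All inputs are assumptions, since the article gives no order delay and no mortality:
- Half of the patients are destined for DZHJTI, independently of prognosis.
- The order delay after admission is exponential with mean d = 1, 3 or 7 days, and DZHJTI can start only within a 14-day stay.
- 6-month mortality is m = 5% or 10%; a share s = 30% or 50% of deaths is spread evenly over the first 14 days.
- Patients who die before an order count as unexposed.

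Let q = 1 − exp(−14/d), the chance that the order comes within the stay, and e = 1 − (d/14)·q, the chance that it precedes an early death. Then:
- exposed deaths = 0.5·m·[s·e + (1 − s)·q]
- exposed survivors = 0.5·(1 − m)·q
- everyone else is a control.

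Example with m = 0.05, s = 0.5, d = 3: q = 0.9906 and e = 0.7877. Exposed deaths are 0.5 × 0.05 × (0.5 × 0.7877 + 0.5 × 0.9906) = 0.02223, and exposed survivors 0.5 × 0.95 × 0.9906 = 0.47054. Exposed risk is 0.02223/0.49277 = 0.0451. Control risk is (0.05 − 0.02223)/(1 − 0.49277) = 0.0547. The ratio is 0.82, where the true value is 1.

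A simulation of 2 million patients per scenario agrees with the formula to about 0.01:

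| m | s | delay 0 | mean 1 day | mean 3 days | mean 7 days |
|---|---|---|---|---|---|
| 5% | 30% | 0.997 | 0.970 | 0.894 | 0.851 |
| 5% | 50% | 0.994 | 0.936 | 0.819 | 0.734 |
| 10% | 30% | 1.001 | 0.958 | 0.890 | 0.846 |
| 10% | 50% | 0.999 | 0.940 | 0.835 | 0.756 |

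The bias vanishes when exposure is fixed at time zero. If patients who die before an order are instead never enrolled, and controls are only those never destined for DZHJTI, the control risk is m. The example becomes 0.0451/0.05 = 0.90, and the same formula gives about 0.98 to 0.84 over the table: smaller, in the same direction.

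**3. Primary outcome with no drug effect.** Take 8.75% ineffective, the control rate under Sample Size. That rate is described there as no change and deterioration, without death, so placing deaths inside it is a further assumption.
- If 10%, 30% or 50% of failures are in-hospital deaths, mean delays of 1 to 7 days give ratios of 0.981 to 0.951, 0.962 to 0.855 and 0.938 to 0.750, in favour of DZHJTI.
- With no deaths, but good recoverers discharged on days 3-14 and the others on days 7-21, patients who recover and leave before an order become controls. The ratios are 1.009, 1.152 and 1.391 at mean delays of 1, 3 and 7 days, against DZHJTI.

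The direction therefore depends on which process dominates.

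**4. Does the stated analysis remove it?** In part 2 being destined for DZHJTI is unrelated to prognosis. There is no confounding to adjust for, yet the ratio is below 1. Weighting on baseline covariates leaves that ratio where it is, and a sensitivity analysis for unmeasured confounding addresses a different problem.

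**The case against.** The strongest reply is that the mechanism is inferred. No sentence says that a patient who dies before an order is counted as a control; such a patient might never be enrolled, and orders might all be written at admission. That stands: the first reading must not be presented as the article's rule, and with all orders at admission the bias is about nil. It does not remove the risk, because nothing in the text ties the order to admission and the alternative enrolment reading still favours DZHJTI for mortality.

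Second, a reader might infer from death counting as failure that the primary outcome is biased towards DZHJTI. The documents do not support a fixed direction. Table 1 schedules the NIHSS only at admission and discharge, and early recovery with discharge before an order pushes the other way.

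Third, Follow-Up Procedures is the operative Methods text and gives one origin, stroke onset; the Abstract and Discussion are summary and narrative. Under that section alone, visits do fall at comparable disease times. Still, the three statements cannot all hold. Stroke onset as a visit clock also does not align the groups on exposure, because DZHJTI can start only after admission.

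Fourth, an analysis plan exists and is not shown; it may set an index date, a landmark or a time-varying exposure. Their absence from the article is therefore not the fault. The fault is what the article does state: conflicting origins, and exposure defined by receipt against an admission baseline.

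Last, the exclusion of controls "who used other dosage forms of Dazhu hongjingtian injection (tablets, capsules" and similar) might be read as removing controls for use after enrolment. That is strained: it is an exclusion criterion in the past tense, and Table 1 places the eligibility screen at admission.

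**Conclusion.** The contradiction in time origin is certain on the text and must be reconciled. The lack of an aligned time zero for exposure is a real risk to the mortality comparison, in favour of DZHJTI unless all orders are made at admission. Its illustrative size, with no true effect, is a 6-month mortality ratio of about 0.97 to 0.73 for mean delays of 1 to 7 days. That range assumes 5-10% mortality, 30-50% of deaths in the first 14 days, and pre-order deaths counted as controls. None of these inputs is in the article, so the range shows sensitivity and is not an estimate for this cohort. For the primary outcome the conclusion is a possible selection bias of uncertain direction.

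**What to change.** - State one time origin, the same for both groups, in the Abstract, Follow-Up Procedures and Discussion, and count the 1-, 3- and 6-month visits from it.
- Record the DZHJTI start date explicitly. The article says that in-hospital administration will be documented, but does not say that this includes the start date.
- Choose one way of aligning exposure. One is to classify exposure at the common origin. Another is to classify it within a fixed window, with a landmark at its end applied equally to both groups. A third is to enter DZHJTI as a time-dependent exposure in the Cox analysis. Clone-censor-weighting is a further option.
- State how patients who die or are discharged before an order are handled in the primary outcome.

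The cost is protocol and analysis-plan wording, one date field if it is not already captured, and some extra analysis. A landmark drops patients who die, or are discharged, before it, so its result applies to those still in hospital at that point; the numbers dropped should be reported by group.

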### Data Collection and Monitoring

Trained research personnel at each participating site will collect baseline data during patient admission, including prehospital care and treatment, prestroke symptoms, and the NIHSS. They will also conduct assessments using the prestroke modified Rankin Scale scores and Barthel Index. Patient information, including demographics, medical and family history, physical examination, auxiliary examination, risk factor assessment, and clinical diagnosis, will be obtained from medical records. The classification of stroke etiology, related complications, and new cerebrovascular events will be documented, and the etiology of AIS will be determined according to the Trial of Org 10172 in Acute Stroke Treatment criteria [17]. Besides standard therapies, the administration of DJHJTI during hospitalization will be documented by the research team.

The collection and reporting of data will use a secure electronic data capture (EDC) system that follows the current clinical protocol and provides each patient with a unique ID. Authorized research personnel can access the EDC system both on personal computers and smartphones, enabling them to complete data collection during daily ward rounds. An overview of the measurement data collection schedule is shown in Table 1. In the EDC system, personal identifiers such as names, ID numbers, and contact information are removed or replaced with unique codes to ensure participant anonymity.

**Table 1 table1:** Schedule of assessments in the cohort study.

Participant assessment	Time point and form				
	Baseline (acute phase)		Follow-up 1	Follow-up 2	Follow-up 3
	Admission	Discharge	1 month	3 months	6 months
	Visit	Visit	Visit or telephone interview	Visit or telephone interview	Visit or telephone interview
Eligibility screen	✓^a^				
Informed consent	✓				
Demographic and anthropometric data	✓				
TCM^b^ questionnaire	✓				
NIHSS^c^	✓	✓			
mRS^d^	✓	✓	✓	✓	✓
BI^e^			✓	✓	✓
Laboratory examination	✓	✓	+^f^	+	+
Imaging examination	✓	✓	+	+	+
Admission status		✓			
Discharge status		✓			
Follow-up interview			✓	✓	✓
AE^g^		+	+	+	+
Outcomes		+	+	+	+

^a^Required data.

^b^TCM: traditional Chinese medicine.

^c^NIHSS: National Institutes of Health Stroke Scale.

^d^mRS: modified Rankin Scale.

^e^BI: Barthel Index.

^f^Optional data to be collected based on the actual occurrence of related events in patients.

^g^AE: adverse events.

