### Outcomes

In this study, the primary outcome will be the distribution of scores on the NIHSS before and after treatment among patients. Secondary outcomes will be assessed at different follow-up visits and will include death, a composite of new clinical vascular events, neurological function, and improvement of traditional Chinese medicine syndrome. Safety assessment will be performed by monitoring adverse events. The complete study outcomes are illustrated in Table 2.

**Table 2 table2:** Outcome variables and definitions.

Outcome variables		Definitions

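### Table 1 schedules the only post-treatment NIHSS at an undated discharge, so the two groups may be scored after different recovery times, with a bias of unknown direction and size

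*Protocol article*

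**What the plan says.** All references are to the Protocol article.

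- **Schedule (Data Collection and Monitoring, Table 1).** The NIHSS row is ticked at admission and discharge and is blank at 1, 3 and 6 months. Admission and discharge share the heading "Baseline (acute phase". No day or window is attached to discharge.
- **Primary outcome (Outcomes).** "the primary outcome will be the distribution of scores on the NIHSS before and after treatment among patients". Table 2 turns this into classes of percentage change. A fall of about 18% separates effective from ineffective, and death counts as ineffective.
- **Primary outcome (Abstract, Methods).** "The primary outcome will be the change in the National Institute of Health Stroke Scale score from baseline to outpatient follow-up". The Abstract's Objective names the same interval.
- **Later visits (Follow-Up Procedures).** "Research personnel will conduct regular face-to-face or telephone follow-up at 1, 3, and 6 months after stroke onset". Table 1 ticks the mRS and Barthel Index at these visits, but not the NIHSS.
- **Exposure.** Under Treatment Regimens, "The administration and dosage of DZHJTI will be determined by the attending physicians based on the patients’ medical history and clinical manifestations". Under Data Collection and Monitoring, "the administration of DJHJTI during hospitalization will be documented by the research team".
- **Analysis (Statistical Analysis).** AIPW balances confounders of exposure, multiple imputation handles missing covariates, and a sensitivity analysis addresses unmeasured confounding.

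**The concern.** The primary comparison needs a before and an after score separated by a comparable interval in both groups. As scheduled, the after score falls on whatever day the patient leaves hospital. That day follows the decision to give DZHJTI. It can be moved by an inpatient course of injections, by recovery itself or by complications. Treatment is not randomised, so nothing in the design makes the interval equal between groups.

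Neurological scores are still changing at this stage; the Discussion says so in its own terms: "since AIS neurological function recovery is a slow process, with the main recovery period occurring within 2 to 6 months after onset". If one group is scored systematically later or earlier, its effective rate can differ without any drug effect. This affects the primary outcome, and it cannot be repaired at analysis, because a score at a common time would never have been collected.

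**Working it through.** The documents state no figure on this point, so there is none to reproduce. The check sets the passages side by side and then adds an illustration on assumed inputs.

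**1. Which post-treatment NIHSS exists?** Table 1 offers discharge only. The Outcomes section gives no time point for the after score, and it links only the secondary outcomes to the follow-up visits. The Abstract's outpatient NIHSS has no counterpart in Table 1, and the later visits may be by telephone. On the schedule as it stands, the primary outcome is read at discharge.

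**2. Is that a common time?** No. Discharge has no fixed day, and it follows an exposure that the physician decides on and that is recorded during the hospital stay.

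**3. Does the stated analysis repair it?** AIPW balances what precedes exposure. Time to assessment comes after exposure, so balance at admission does not equalise it. Adjusting for length of stay would condition on a variable that treatment and recovery may both affect. The sensitivity analysis for unmeasured confounding addresses a different problem.

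**4. How small a shift can matter?** NIHSS 0-5 is excluded, so baseline is at least 6. For baselines 6 to 11 the 18% cut lies between 0.18 × 6 = 1.08 and 0.18 × 11 = 1.98 points. A fall of two whole points therefore decides the class.

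**5. Illustration only (no drug effect).**

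Inputs from the documents:
- Control ineffective rate 8.75% (Sample Size).
- Cut at 18% (Table 2).
- 1000 per group less 20% dropout = 800 evaluable per group (Sample Size).

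Assumed inputs, not in the documents:
- Fractional fall at day *d* = *A*·(1 − exp(−*d*/τ)), with τ of 7 to 21 days.
- *A* normal with SD 0.20 to 0.30.
- Controls scored at day 10, with the mean of *A* set so that 8.75% fall by less than 18% on that day.
- The same recovery curve in both groups, unrelated to the discharge day.

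One case, SD 0.25 and τ = 14:
- Day 10: 1 − exp(−10/14) = 0.5105, and 0.18/0.5105 = 0.3526. The mean of *A* is 0.3526 + 0.25 × 1.356 = 0.692.
- Treated scored at day 12: 0.18/0.5756 = 0.3127, z = (0.3127 − 0.692)/0.25 = −1.52, ineffective 6.5%.
- Treated scored at day 8: 0.18/0.4353 = 0.4135, z = (0.4135 − 0.692)/0.25 = −1.11, ineffective 13.3%.

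Across the assumed grid, against 8.75% in controls:

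| Treated scored | Ineffective rate | Difference in percentage points | Chance of a significant result, 800 per group |
|---|---|---|---|
| 2 days earlier | 10.3%-18.7% | 1.6-9.9 higher | about 18% to nearly 100% |
| 2 days later | 4.8%-7.9% | 0.9-4.0 lower | about 9%-88% |
| 4 days later | 3.0%-7.3% | 1.4-5.8 lower | about 18%-99.8% |

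With scoring at the same time in both groups, the artefact in this model is zero. The width of the ranges and the change of sign show how little the documents constrain the answer. The table is not an estimate for this study.

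**The case against.** **No difference in stay is documented.** A reader might infer that DZHJTI patients stay longer and so look better. The documents do not support this. They give no course length, no length of stay and no effect of the injection on stay. The direction is also open. If recovery triggers discharge, a long stay marks slow recovery and scores at discharge tend to converge. If complications prolong stay, longer-stay patients look worse. A longer stay also leaves more time for an in-hospital death, which Table 2 counts as ineffective. This objection stands against any one-directional claim. It does not make the assessment times equal.

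**The size is conjecture.** A reader might assume 0.1, 0.2 or 0.3 points of recovery per day and 2, 4 or 7 extra days, giving 0.2 to 2.1 points. Only one of those nine products (0.3 × 7 = 2.1) exceeds 1.44, which is 18% of an assumed baseline of 8. The Discussion's statement that most recovery comes at 2 to 6 months also argues against a large gain over a few ward days, and it fits poorly with the τ values assumed above. This stands: no magnitude can be claimed.

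**The primary NIHSS may be meant for an outpatient visit.** If so, the point falls away for the primary outcome once Table 1 is corrected. This stands, and it makes the point conditional.

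**Disability is measured at common times.** The mRS and Barthel Index are scheduled at 1, 3 and 6 months. That limits the consequence for the study as a whole, but these are secondary outcomes and do not cure the primary one.

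**Windows and timing analyses belong in the full protocol or SAP.** That is fair for windows. But an analysis plan cannot supply a common-time NIHSS if the schedule does not collect one.

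**Conclusion.** The point holds as a conditional weakness of design. On Table 1 as written, the primary outcome depends on an NIHSS taken on an unfixed day after exposure, and the two groups may be scored after different recovery times. The stated AIPW on baseline confounders does not remove a bias of this kind.

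The direction and size are unknown. The conclusion rests on two things: the schedule itself, and the possibility, not documented as fact, that discharge day differs between groups. It also depends on how the Abstract's outpatient time point is reconciled with Table 1. The change is worth making because it is cheap and cannot be made after the data are collected.

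**What to change.** **First, reconcile** the Abstract (Objective and Methods), the Outcomes section and Table 1 on when the primary NIHSS is taken.

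**If a fixed outpatient visit is meant:** schedule an in-person NIHSS there in Table 1 and name the clock it runs from. The Abstract counts follow-up from the start of medication, Follow-Up Procedures from stroke onset, and the Discussion from discharge. A clock started at discharge would bring the timing problem back. The cost is that this visit can no longer be done by telephone.

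**If the in-hospital score is meant:**
- Schedule and date one NIHSS on a single prespecified day from baseline in both groups, taking the discharge score for patients discharged earlier.
- Use that score for the primary comparison and keep the discharge NIHSS as descriptive.
- Report days from admission to assessment by group.
- Add a sensitivity analysis for patients discharged before the fixed day.
- Move discharge out from under the baseline heading in Table 1.

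The cost is one extra short bedside scale, done by trained personnel who already collect data on daily ward rounds. The remaining weakness is that early-discharged patients still contribute a score at a time that may depend on their recovery. The bias is therefore reduced, not removed.
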